## 1.0 BACKGROUND AND SCIENTIFIC RATIONALE

### 1.1 Summary

Therapeutic blockade of immune checkpoint molecules has induced clinical benefit for patients with several cancers. In counterbalance to checkpoint molecules are a set of costimulatory molecules, including CD27. CD27 contributes to activation and survival of T cells; fully stimulated T cells may be resistant to deletion by checkpoint inhibitors. Notably, CD27-stimulation lowers expression of inhibitory molecules on CD8+ T cells, and reduces the frequency of regulatory T cells (Treg) in the tumor microenvironment (TME). Our experience with a fully human agonistic CD27 antibody (CDX-1127/Varlilumab, Celldex) indicates it is safe and bioactive in cancer patients when delivered systemically: it increases frequencies of activated (HLA-DR+) CD8+ T cells and CD56lo NK cells, while the proportion of Tregs is decreased (NCT01460134). In a murine model, a CD27 antibody enhanced the immunologic benefit and tumor control induced with a tumor vaccine. Thus, there is rationale for studying immunologic effects of agonistic antibodies to CD27, in combination immunotherapy with cancer vaccines. The present clinical trial will test the safety and immunologic outcomes of administration of an agonistic antibody to CD27 in conjunction with an antigen vaccine: an enhanced helper peptide vaccine, 6MHP. The present proposal will test the hypotheses that agonism of CD27 systemically, in conjunction with a TLR agonist, is safe and augments vaccine efficacy by optimizing T cell induction, improving T cell survival, and decreasing regulatory T cells.

Amendment to reduce vaccine site ulceration (12-03-2020): Three vaccine site ulcerations meeting criteria for DLTs were observed by 11/23/20, one on arm A and two on Arm B. There was no evidence that the CD27 Ab contributed to this risk. The study was held once earlier for DLTs on arm B which included a grade 3 pneumonitis and was reinitiated after review with the DSMC and modification to the study exclusion criteria. The second DLT, vaccine site ulceration on Arm B, required an additional study hold resulting in a study modification to reduce vaccine site ulceration by administering vaccines subcutaneously only, by limiting to 5 vaccines, and by removing the vaccine site biopsy at week 12.

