### 7.4 **Safety Monitoring**

Toxicities will be monitored using CTCAE 5.0 criteria, with additional recording of immune-related adverse events (irAE). Stopping rules will be based on expected DLT rates discussed in [Section 7.1.1](#) for each of the combination arms. Significant increases over the reported rates are not expected but would be a reason for early discontinuation. Thus, formal safety bounds based upon the observed number of participants who experience a DLT as defined in [Section 8.9](#) will guide decisions about early stopping due to potential safety concerns. If a stopping bound is crossed then accrual to the study will be suspended until the study PI, co-investigators, sponsors and the DSMC can review the data, and determine if the study should continue, be amended or be closed to further accrual. The rate of DLTs will be monitored up to 30 days after the last vaccination. A sequential probability ratio test (SPRT) based upon a binomial test of proportions for DLTs will be used. Only the upper boundary will be used for monitoring to protect against excessive failure rates. The stopping boundary are for a SPRT contrasting a 5% versus 25% DLT rate, with nominal type I and II errors of 10% and 10%, respectively.

Stopping guidelines have triggered two study reviews and amendments. Upon approval of treatment change in Protocol v12-03-2020, the monitoring stopping guidelines will be applied separately to the subset of participant's accrued pre and post approval of Protocol v12-03-2020.

| Table 10: Stopping Guidelines for DLTs                        |          |
|----------------------------------------------------------------------|----------|
| Number of participants pre and post approval of Protocol v12-03-2020 | Boundary |
| 2-6                                                                  | $\geq 2$ |
| 7-14                                                                 | $\geq 3$ |
| 15-16                                                                | $\geq 4$ |

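### The DLT stopping rule is described only by nominal 10%/10% error rates; as truncated and split, a single count misses a 25% DLT rate 24% to 53% of the time at 7 to 16 participants

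*Combined protocol and SAP*

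**What the plan says.** Section 7.4 sets up the rule in these terms: "A sequential probability ratio test (SPRT) based upon a binomial test of proportions for DLTs will be used". The boundary comes from an "SPRT contrasting a 5% versus 25% DLT rate, with nominal type I and II errors of 10% and 10" percent, and "Only the upper boundary will be used for monitoring to protect against excessive failure rates". Under "Table 10: Stopping Guidelines for DLTs", the trigger is at least 2 DLTs at 2 to 6 participants, 3 at 7 to 14 and 4 at 15 to 16, where the table ends.

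The amended text adds that "the monitoring stopping guidelines will be applied separately to the subset of participant's accrued pre and post approval of Protocol v12-03-2020".

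The unit of counting is not settled. Section 7.4 speaks of expected DLT rates "for each of the combination arms", and Section 1.1 describes a past hold by arm: "The study was held once earlier for DLTs on arm B which included a grade 3 pneumonitis". Both suggest counting by arm. The Table 10 row label mentions only the pre and post subsets.

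Section 7.5 calls the bounds non-binding. The text available gives no crossing probability at 5% or 25% for the rule as applied.

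**The concern.** DLTs are the endpoint of the first primary objective, and Section 7.4 is the only formal criterion applied to them during the trial. Its only stated error rates are the two nominal 10% figures. A Wald test approximates such rates when it runs, with both boundaries, until one is reached. Here each count ends when its subset is full, and the amendment made the subsets shorter. The error statement was not restated for the shorter counts.

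At stake is how an uncrossed boundary is interpreted, particularly in the post-amendment subset, where the changes made to reduce vaccine-site ulceration are being tried. A reader who relies on the stated type II error would treat non-crossing in that subset as about 90% assurance against a 25% DLT rate. The short counts do not give that.

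**Working it through.** **Inputs from the documents.** p0 = 0.05, p1 = 0.25, α = β = 0.10, upper boundary only (Section 7.4); maximum accrual 34, target 30 evaluable (Section 7.2); 1:1 allocation (Section 7.3).

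**Assumed counts.** The heading of Section 1.7 refers to the first 15 participants, and the 12-03-20 entry in Section 9.6 says that section was added with the amendment. I take about 15 before the amendment and up to 34 − 15 = 19 after. By arm that is 7 and 8 before, and 9 and 10 after. The text available states no exact pre-approval count.

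**Step 1: reproduce Table 10.** Stop when the number of DLTs x satisfies

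x ≥ [ln((1−β)/α) + n·ln((1−p0)/(1−p1))] / ln[p1(1−p0)/(p0(1−p1))]

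= [2.197 + 0.2364n] / 1.846 = 1.190 + 0.128n, rounded up.

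This gives 2 for n = 2–6, 3 for n = 7–14 and 4 for n = 15–21. Table 10 is reproduced exactly.

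**Step 2: crossing probabilities for one count.** Let q(n, x) be the probability of x DLTs after n participants with no crossing so far. Then q(n, x) = (1−p)·q(n−1, x) + p·q(n−1, x−1), dropping every x at or above the boundary. The miss probability at N is the sum of what remains. This assumes a look after each participant with complete DLT data.

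Hand check at p = 0.25: through n = 6 the path survives only with 0 or 1 DLT, so the miss is 0.75⁶ + 6(0.25)(0.75⁵) = 0.178 + 0.356 = 0.534. At n = 7 the trigger rises to 3, which a surviving path cannot yet reach, so the miss stays at 53.4%.

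| Participants in one count | Crosses at true 5% | Never crosses at true 25% |
|---|---|---|
| 7 | 3.3% | 53.4% |
| 8 | 3.3% | 51.2% |
| 9 | 3.5% | 47.6% |
| 10 | 3.6% | 43.2% |
| 15 | 5.0% | 25.1% |
| 16 (last tabulated) | 5.1% | 24.2% |
| 19 (line extended) | 5.3% | 18.7% |

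The miss rate first reaches 10% or less at n = 28 in a single count (9.05%; it is 10.2% at n = 27).

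**Step 3: locate the cause.** The full two-boundary test with no truncation has exact errors of 5.9% and 8.9%, so the nominal figures are reasonable for that test. Adding the lower boundary to the truncated rule leaves the miss unchanged at n = 7–10 and raises it slightly later: 24.6% against 24.2% at 16, and 19.7% against 18.7% at 19. Omitting the lower boundary is therefore not the cause. Short counts are.

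**Step 4: the trial as a whole, on the assumed counts, treated as independent.**

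- True rate 5% throughout, at least one crossing: pooled, 1 − (0.9497 × 0.9469) = 10.1%. Four arm-by-period counts, 1 − (0.9672 × 0.9666 × 0.9655 × 0.9636) = 13.0%.
- True rate 25% throughout, no count crosses: pooled, 0.2514 × 0.1873 = 4.7%. Four counts, 0.5339 × 0.5117 × 0.4755 × 0.4317 = 5.6%.
- One arm at 25% in both periods, neither of its counts crosses: 0.5339 × 0.4317 = 23.1% (7 then 10), or 0.5117 × 0.4755 = 24.3% (8 then 9).

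**The case against.** The best defence is that nothing has been miscalculated. Table 10 follows from its inputs, and the plan itself calls the errors nominal, meaning design inputs. That stands: the gap is in reporting, not in the boundary.

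Second, per-count figures are not the trial's figures. If the rate were 25% in every count, some count would cross about 94% to 95% of the time. This also stands, and it cuts both ways: describing the type I error as about 5% without a per-count label would understate a trial-wide false-alarm chance of 10% to 13%. It does not rescue the single-count statement, because an excess confined to the post-amendment regimen, or to one arm, is seen only by the counts that contain it.

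Third, the 53% figure belongs to a count of 7, a pre-amendment arm whose accrual is over. Looking forward, the per-arm range is 43% to 48%, on the assumed counts.

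Fourth, the practical consequence is limited. The bounds are non-binding, they have already triggered two reviews, and Section 8.13.1 has the DSMC meeting monthly with all adverse events in its remit. A missed crossing does not mean that no one looks.

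Two stronger inferences should be resisted. A reader might infer that the DSMC has been told the rule catches a 25% rate nine times in ten; no section says so, although the only stated type II error invites it. A reader might also infer that Table 10 is incomplete because it ends at 16. That matters only if arms are pooled and accrual approaches 34. With per-arm counts, or a pooled total of 30 with 15 already enrolled, 16 is not exceeded.

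**Conclusion.** The point holds as a gap in the stated operating characteristics. No single count below 28 delivers a 10% type II error, whichever way the counting is read. Within Table 10, with no extrapolation, the miss rate at 25% is at least 24%. If counting is by arm within period, it is 43% to 53%. Crossing at 5% occurs 3% to 5% of the time per count, below nominal, so only the type II side is understated for a single count.

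The 24% and 25% figures need only Table 10, a look after every participant and complete DLT data; fewer looks or late-reported DLTs would raise them. The 7-to-10 and trial-wide figures also rest on the inferred split of 15 and 19, and the trial-wide ones on independence between counts.

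The documents do not support saying that the boundary is wrong, that using only the upper boundary weakens detection, or that the trial as a whole would miss a uniform 25% rate a quarter to half of the time.

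**What to change.** In Section 7.4, replace or supplement the nominal statement with exact crossing probabilities at 5% and 25% for the counts actually monitored, labelled per count, and give the trial-wide figures beside them. Use the real pre-amendment enrolment in place of the 15 assumed here.

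State whether Table 10 counts each arm or both arms together. If pooled, continue the same computed line past 16; the value 4 holds for n = 15–21.

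Do not describe non-crossing in one count as 90% assurance against a 25% rate.

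The cost is a few sentences and, if pooled, one extended table row. No boundary value changes and no new data are needed. The stated per-count detection becomes less favourable.

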### 7.5 **Analyses**

Study populations and evaluation criteria are noted in [Section 7.1](#). Adverse events will be summarized by frequency and magnitude of event. Incidence of DLTs will be monitored against the safety bounds above. The bounds are non-binding, and provide a guideline that may result in study modification or closure.

A 5-fold or greater CD4+ Th1 memory response to vaccine antigens compared to baseline is consider a response. Amounts less than 5-fold are considered as a non-response. Immune and clinical endpoints are defined in [Section 7.1.2](#) and in [Section 7.1.3](#), respectively. Time to event measures (DFS and OS) will be estimated by the methods of Kaplan and Meier.

This study is designed to estimate differences and not to make statistical comparisons between arms. All CD4+ T cell and CD8+ T cell ELISpot results will be assessed relative to the participant specific baseline measure with graphical representation of measures over time. The difference in the proportion of participants considered to have a durable response between arms will be estimated and a 90% confidence interval around the difference, using the score method of Miettinen and Nurminen. Similarly, the difference in

the proportion of participants considered to have a memory response at day 183 between arms will be estimated and a 90% confidence interval around the difference calculated. In addition, repeated measure models will be explored to estimate difference in patterns of response between arms over time for CD4+ T cell, CD8+ T cell and percent of circulating Tregs (with a log10 transformation). Within an arm, for each participant, the difference in amount of FoxP3+ cells in the vaccine site microenvironment at weeks 3 and 12 (for those with biopsies done on week 12) will be calculated. Estimated difference in mean change by arm with 90% CI estimates around the difference in means will be used to estimate potential differences by arm.

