### 7.1.2 **Immunogenicity**

All eligible participants receiving any protocol defined treatment who have at least two evaluable blood draws (including baseline) for immune analyses will be evaluated for the following immune response parameters. In addition, all

participants are considered 'evaluable' for the primary endpoint if they have been evaluated for immune response at baseline and at least day 127; or they have progressed prior to the day 127 assessment; or have stopped treatment due to DLTs.

In PBMC:

- CD4+ Th1 response to vaccine antigens by ELIspot:
  - Magnitude of response at all times
  - Frequency of response over time
  - Persistence of response over time
- Circulating regulatory T cells (Tregs) as measured by flow cytometry over time
- CD8+ T cell responses to peptides not in the vaccine over time
- CD4+ T cell activation versus exhaustion
  - Activation measured by an increase in %DR+ CD4+ cells of total CD4+ cells
  - Exhaustion measured by increase in the % of DR+CD4+ T cells that co-express both PD-1 and either LAG3 or TIM3.

In the tumor microenvironment:

- FoxP3+ CD4+ T cells per mm^2 in vaccine site biopsies by immunohistochemistry and gene expression analysis at weeks 3 and 12. **Note:** with revision to reduce ulceration at vaccine sites, biopsies are not required at week 12 for participants whose week 12 visit would be due after IRB approval of Protocol v12-03-2020.

In serum:

- IgG antibodies to 6MHP by ELISA for IgG over time

A CD4+ T cell response to 6MHP (Rsp), is defined as all of the following, based on direct ELIspot assay:

- a) an increase of at least 20 IFN-gamma secreting cells per 100,000 CD4+ T cells, over the maximum of the negative controls ( $T_{\text{neg cctrl}}$ )
- b) no overlap in standard deviations between the response to 6MHP peptide pool ( $T_{\text{vax}}$ ) and  $T_{\text{neg cctrl}}$
- c) the ratio of  $T_{\text{vax}}$  to  $T_{\text{neg cctrl}}$  at one or more time points, after week 0, is at least 5-fold the prevaccine ratio of  $T_{\text{vax}}$  to  $T_{\text{neg cctrl}}$ . Note that any prevaccine ratio of  $T_{\text{vax}}$  to  $T_{\text{neg cctrl}}$  below 1 will be set to 1 to avoid overinflating that ratio.

A durable response (dRsp) is defined as a Rsp detected over at least two consecutive time periods during vaccination (days 8 through 85).

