A persistent response (pRsp) is defined as a dRsp plus a Rsp detected on day 127 or 176.

A memory recall (mRsp) is defined as a Rsp detected at any time point from day 8 through day 85, and a Rsp on day 183 compared to the Rsp on day 176, with all of the following:

- a) an increase of at least 20 IFN-gamma secreting cells per 100,000 CD4+ T cells over  $T_{\text{neg cctrl}}$  at day 183.
- b) no overlap in standard deviations between  $T_{\text{vax}}$  and  $T_{\text{neg cctrl}}$  at day 183.

- d) at least a 2-fold increase in the ratio of  $T_{\text{vax}}$  to  $T_{\text{neg cntrl}}$  compared to the ratio of  $T_{\text{vax}}$  to  $T_{\text{neg cntrl}}$  at day 176. Note that if that ratio at day 176 is below 1, it will be set to 1 to avoid overinflating response assessment at day 183.

Evaluable participants who have progressed prior to the day 127 assessment or have stopped treatment due to DLTs will be considered response failures for dRsp, pRsp and mRsp.

Measures of CD8+ T cell responses by ELISpot will use the same criteria defined above, except that that definition of response will be based on response to peptides restricted by Class I MHC molecules, and the data will be normalized to the number of CD8+ T cells in the assays (eg: criterion of at least 20 IFN-gamma secreting cells per 100,000 CD8+ T cells over  $T_{\text{neg cntrl}}$ ).

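### Section 7.5 classifies a memory response by a 5-fold rule against baseline that does not match the mRsp definition in Section 7.1.2

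*Combined protocol and SAP*

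**What the plan says.** Section 7.1.2 (Immunogenicity) first defines a general response, Rsp, by three criteria. The third, criterion c), requires that the ratio of vaccine-stimulated to negative-control counts "is at least 5-fold the prevaccine ratio of" the same quantities.

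It then defines mRsp. The participant needs an Rsp at some point from day 8 to day 85, "and a Rsp on day 183 compared to the Rsp on day 176, with all of the following": a margin of 20 or more secreting cells per 100,000 over control, no SD overlap, and "at least a 2-fold increase in the ratio of" vaccine to control counts, judged against day 176. There is a floor on the reference value: "Note that if that ratio at day 176 is below 1, it will be set to 1". The three items are lettered a, b and d; there is no c.

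Section 7.5 (Analyses) says "A 5-fold or greater CD4+ Th1 memory response to vaccine antigens compared to baseline is consider a response", and then "Amounts less than 5-fold are considered as a non-response". These sentences name neither day 176 nor a doubling. The next sentence begins "Immune and clinical endpoints are defined in" and refers to Section 7.1.2 for the immune endpoints. The following paragraph plans the analysis: the difference in the proportion "considered to have a memory response at day 183 between arms will be estimated and a 90% confidence interval around the difference calculated".

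Secondary objective 2d (Section 2.2) places the endpoint one week after the booster and gives neither a fold threshold nor a reference time.

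**The concern.** The two sections label participants as memory responders by rules that differ in threshold (5-fold against 2-fold) and in reference time (baseline against day 176). Taken literally, the 7.5 sentences also drop the earlier-response, 20-cell and SD conditions. If the analyst follows 7.5, a response that is merely held through the booster counts as memory. If the analyst follows 7.1.2, it does not count unless the ratio doubles.

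At stake is the numerator in each arm for a planned between-arm estimate. The trial is open-label, so it is better to settle the rule before the day-183 data are classified than to leave it to interpretation afterwards.

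**Working it through.** The plan gives no assumed rate, power or sample size for mRsp, so there is no figure to reproduce. The check applies both rules to hypothetical profiles.

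**Inputs.** Thresholds, reference times and the floor of 1 come from Sections 7.1.2 and 7.5. The 15 per arm comes from the Accrual Goal in the synopsis. The following are assumed: baseline ratio 1, control count 10 per 100,000, an earlier Rsp between days 8 and 85 (ratio 6), and no SD overlap.

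**Formulas.**
- 7.5 fold = day-183 ratio / baseline ratio; response if 5 or more.
- 7.1.2 fold = day-183 ratio / day-176 ratio (floored at 1); needs 2 or more, plus day-183 count minus control of 20 or more.
- 7.1.2 can be read two ways at day 183: items a, b and d only, or those plus general criterion c), brought in by the defined term Rsp.

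| Day 176 ratio | Day 183 ratio | Net cells, day 183 | Fold over baseline | Fold over day 176 | 7.5 | 7.1.2 (a, b, d) | 7.1.2 (plus c) |
|---|---|---|---|---|---|---|---|
| 6 | 6 | 60 − 10 = 50 | 6.0 | 1.0 | yes | no | no |
| 4 | 6 | 50 | 6.0 | 1.5 | yes | no | no |
| 6 | 8 | 80 − 10 = 70 | 8.0 | 1.33 | yes | no | no |
| 2.5 | 6 | 50 | 6.0 | 2.4 | yes | yes | yes |
| 1.5 | 4 | 40 − 10 = 30 | 4.0 | 2.67 | no | yes | no |

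The first three rows conflict on both readings of 7.1.2. The last row conflicts only if criterion c) is not required at day 183.

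**Grid.** Day-176 ratios from 1 to 10 and day-183 ratios from 1 to 20, in steps of 0.5, give 19 × 39 = 741 pairs. On the a, b, d reading, 240 are responders under 7.5 only, 10 under 7.1.2 only, 349 under both and 142 under neither. Adding criterion c) removes the 10 and leaves the 240. These counts show where the rules part; they are not probabilities.

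**Scale.** One reclassified participant moves an arm's rate by 1/15 = 6.7 percentage points. As an illustration with hypothetical counts, using the Miettinen–Nurminen score interval that 7.5 names for the durable-response difference: 7/15 against 2/15 gives 33.3 points (90% CI 5.6 to 57.0), and 6/15 against 2/15 gives 26.7 points (90% CI −0.4 to 50.9). One classification is enough to move the lower bound across zero in that example.

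**The case against.** The strongest reply is that 7.5 itself sends the reader to 7.1.2 for the immune endpoints, immediately after the 5-fold sentences. On that view they are a loose paraphrase of general criterion c) with the word memory misplaced, and 7.1.2 governs. This is plausible, and it means the endpoint is not without a definition. But the pointer gives no precedence, and the sentences name memory response explicitly. Section 7.5 also says that ELISpot results are assessed against each participant's own baseline, which fits the 5-fold sentences better than a day-176 reference. If the sentences are a mislabel, they still need correcting.

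A second reply is that Rsp is a defined term, so an Rsp at day 183 already includes the 5-fold criterion. Then a result below 5-fold is a non-response in both sections. That part stands if the reading is right, and it removes the reverse conflict. It does not remove the main one, because 7.5 treats 5-fold as sufficient while 7.1.2 would need the doubling as well. The lettering a, b, d leaves the reading unsettled.

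Three stronger inferences are tempting and are not supported:
- A reader might infer that both rules are stated for day 183. The 5-fold sentences name no day; the link comes through the shared label and the analysis that follows.
- A reader might infer that the 7.1.2 rule penalises Arm A and the 7.5 rule favours it. With a baseline ratio of 1, someone at 5-fold on day 176 must indeed reach 5 × 2 = 10-fold on day 183 under 7.1.2. But the documents give no data on how the booster response varies with the day-176 level, and CDX-1127 could raise both.
- A reader might infer that the doubling rule is itself a flaw. Section 7.1.2 calls mRsp a memory recall and the sample is taken a week after a booster, so a rise from the pre-booster level is a reasonable target. Persistence has its own primary endpoint, pRsp.

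**Conclusion.** The inconsistency is real and holds on either reading of 7.1.2: a sustained response that is 5-fold or more over baseline, but does not double from day 176, is a memory response in 7.5 and not in 7.1.2. This needs only that the ratios be as in the worked profiles. The reverse disagreement depends on criterion c) not applying at day 183, which the text does not settle.

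The size is 6.7 points on an arm's rate per reclassified participant at 15 per arm. How many participants would be affected, and in which arm, cannot be told from the documents. The consequence is confined to one secondary endpoint in a study that aims at estimation; pRsp, the sample size and the DLT stopping bounds do not depend on it. It should be corrected before analysis because the text as written gives two answers for the same participant.

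**What to change.** 1. Delete the two 5-fold memory-response sentences from Section 7.5, or relabel them as general Rsp criterion c).
2. State in 7.5 that the day-183 memory comparison uses mRsp exactly as defined in 7.1.2.
3. In 7.1.2, state whether criterion c) is also required at day 183, and correct the a, b, d lettering to match.
4. Optionally, report the proportion with an Rsp at day 183 against baseline as a named supportive estimate, so that a response held at a high level remains visible beside recall.

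Items 1 to 3 are wording changes only. Item 4 adds one descriptive line from data already collected. No change to conduct, sampling or sample size is needed.

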**Figure 1: Protocol Schema**

**A**

[figure not shown]

**B**

[figure not shown]

**Figure 1.** Clinical trial design. Patients will be enrolled in a phase I/II design to evaluate the safety and immunologic effects of adding agonistic CD27 antibody CDX-1127 to a cancer vaccine. Patients with stage IIB-IV melanoma at original diagnosis will be eligible, as well as some patients with high-risk stage IIA melanoma by the DecisionDx melanoma or DecisionDX-UM test. Patients will receive the multi-peptide vaccine 6MHP (200 mcg of each melanoma peptide). 6MHP vaccines will be administered with TLR3 agonist polyICLC (Hiltonol) in an emulsion with Montanide ISA-51. Immunologic effects will be assessed in peripheral blood. A booster vaccine (without polyICLC) administered day 176 will permit evaluation of recall memory responses a week later (d183). The study opened with the design shown in **(A)**, but was revised after several patients had dose-limiting vaccine site ulcerations, with 3 changes to reduce the risk of vaccine site ulcerations (i) vaccines all administered subcutaneously rather than half-subcutaneous and half-intradermally, (ii) reduced from 7 to 5 vaccines, and (iii) removed the vaccine site biopsy at week 12, as shown in **(B)**. Participants enrolled after approval of Protocol v12-03-2020 will follow schema B. Participants enrolled prior to the amendment, but who were between week 3 and 12 at the time the amendment was approved will follow the amended schema **(B)**.

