### 2.2 **Secondary Objectives**

- 1) To assess whether CD27 antibody decreases regulatory T cells (FoxP3+ cells) in the vaccine site microenvironment at weeks 3 and 12. [Endpoint: in vaccine site biopsies FoxP3+ CD4+ T cells per mm^2 in by immunohistochemistry and gene expression analysis)] **Note**: with revision to reduce ulceration at vaccine sites, biopsies are not required at week 12 for participants whose week 12 visit would be due after IRB approval of Protocol v12-03-2020.
- 2) To determine whether addition of CD27 antibody to a melanoma vaccine,
  - a) Decreases circulating regulatory T cells [Endpoint: circulating Tregs, % of CD4+ T cells responding to vaccine antigens; FoxP3+ CD4+ T cells as measured by flow cytometry]
  - b) Improves the frequency of CD4+ Th1 responses to vaccine antigens [Endpoint: CD4+ response to 6MHP measured by ELISpot; maximum increase after vaccination at any time point]
  - c) Improves the frequency of durable CD4+ Th1 responses to vaccine antigens (dRsp) [Endpoint: CD4+ response to 6MHP measured by ELISpot; at two

- consecutive time points (day 8 to 85)]
- d) Increases the CD4+ Th1 memory response (mRsp) to vaccine antigens at 6 months. [Endpoint: CD4+ response to 6MHP by ELISpot a week after booster vaccine on day 176]

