### **5.13 Biopsies**

#### Vaccine Site Biopsies

Before Protocol v12-03-2020, each participant had a biopsy of a vaccine site at two time points (days 22 and 85 or End of Treatment). After approval of Protocol v12-03-2020, only the biopsy at day 22 will be done. The biopsy will consist of three 4-mm punch biopsies of skin.

Prior to Protocol v12-03-2020, the vaccine site biopsy at day 85 was required for all participants, except that it was optional for participants who discontinued vaccine therapy before vaccine 6 but did not discontinue varilumab therapy if applicable, and it should not have been done if the participant had ulceration at the vaccine site or had a vaccine-site related DLT.

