## 6.7 **Vaccine Site Biopsies**

### 6.7.1 **Sampling**

Prior to Protocol v12-03-2020, each participant had a biopsy of a vaccine site at two time points (days 22 and 85). After approval of Protocol v12-03-2020, each participant will undergo a biopsy at a vaccine site at day 22 only. The biopsy will consist of three 4-mm punch biopsies of skin. The biopsy will be performed on skin at the site of the most recent vaccine.

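### The only planned vaccine-site FoxP3 comparison between arms is the week 3 to week 12 change, which does not estimate the effect on FoxP3+ level that secondary objective 1 asks about and leaves out participants without a week-12 biopsy

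*Combined protocol and SAP*

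**What the plan says.** Section 2.2 states secondary objective 1 as "To assess whether CD27 antibody decreases regulatory T cells" "in the vaccine site microenvironment at weeks 3 and 12". The endpoint there and in Section 7.1.2 is a density: FoxP3+ CD4+ T cells per mm² in vaccine site biopsies.

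Section 7.5 gives one analysis of that endpoint. For each participant, the difference in FoxP3+ "cells in the vaccine site microenvironment at weeks 3 and 12 (for those with biopsies done on week 12) will be calculated". The arms are then compared through the "Estimated difference in mean change by arm with 90% CI estimates around the difference in means". No comparison of FoxP3+ levels between arms is specified at week 3 or at week 12.

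The availability of the two biopsies differs:

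- **Day 22 (week 3).** Taken in all participants, before and after the December 2020 amendment. Section 6.7.1: "After approval of Protocol v12-03-2020, each participant will undergo a biopsy at a vaccine site at day 22 only".
- **Day 85 (week 12), after the amendment.** Section 7.1.2 says that "biopsies are not required at week 12 for participants whose week 12 visit would be due after IRB approval of Protocol v12-03-2020". The Figure 1 caption applies this to people already enrolled "who were between week 3 and 12 at the time the amendment was approved will follow the amended schema".
- **Day 85, before the amendment.** Section 5.13 says that "it should not have been done if the participant had ulceration at the vaccine site", and the same exclusion covers a vaccine-site DLT.

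Section 5.3.1 places the Arm A doses of CDX-1127 on days 1, 36 and 78. The study calendars in Section 9.1 show no vaccine-site biopsy before treatment.

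**The concern.** The objective is about a level, and the analysis is about a change between two visits that both follow the first CDX-1127 dose. Week 3 is not a baseline. Any effect already present on day 22 is subtracted from the effect on day 85, so the planned contrast can be null, or can point the wrong way, when the antibody does lower FoxP3+ cells.

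An early effect is not far-fetched on the protocol's own rationale. Sections 1.2 and 1.6.1 cite reduced circulating regulatory T cells by day 29 in the phase I trial of CDX-1127. That is blood rather than vaccine site, but the timing is close to the day-22 biopsy.

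The amendment makes matters worse. The change can be computed only for people with both biopsies, and those without a week-12 biopsy drop out of the only vaccine-site FoxP3 comparison. Later participants still undergo three 4-mm punch biopsies on day 22, yet Section 7.5 does not say how their week-3 FoxP3 values would be compared between arms.

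**Working it through.** **What the contrast estimates.** Take change as week 12 minus week 3 (Section 7.5 does not state the direction). Let d3 and d12 be the Arm A − Arm B differences in mean FoxP3+ level at the two visits. Then:

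difference in mean change = d12 − d3

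With illustrative effects in SD units (negative means fewer FoxP3+ cells in Arm A):

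| d3 | d12 | d12 − d3 |
|---|---|---|
| −1 | −1 | 0 |
| −1 | −0.5 | +0.5 |
| −0.5 | −1 | −0.5 |
| 0 | −1 | −1 |

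The contrast equals the week-12 effect only if the week-3 effect is zero. In no row of the table does it equal the week-3 effect except the third, and there by coincidence.

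**Who contributes.** A pair needs a week-12 visit due before the amendment, no ulceration at the vaccine site and no vaccine-site DLT. The last two are post-randomisation outcomes related to local inflammation, so the arms being compared are no longer the arms as randomised. Section 1.1 reports three ulceration DLTs by 11/23/20, one in Arm A and two in Arm B.

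**Precision.** The plan gives no SD, sample size or precision for this endpoint, so there is no FoxP3 figure to reproduce. The overall accrual figure in Section 7.2 does reproduce: 30 / 0.9 = 33.3, rounded up to 34.

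Inputs:

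- 15 per arm evaluable: synopsis, accrual goal. Using it for week 3 assumes that each of them yields an evaluable day-22 biopsy.
- At most 15 pairs: an assumption, taken from the first 15 participants named in the heading of Section 1.7. The documents do not give the number of pairs.
- Within-person correlation r from 0 to 0.7: an assumption.
- A common SD of 1 at each visit: an assumption.

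90% CI half-width = t(0.95, nA + nB − 2) × S × √(1/nA + 1/nB), where S = 1 for one visit and S = √(2(1 − r)) for the change.

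| Analysis | n per arm | r = 0.7 | r = 0.5 | r = 0.3 | r = 0 |
|---|---|---|---|---|---|
| Change | 8 vs 7 | 0.71 | 0.92 | 1.08 | 1.30 |
| Change | 6 vs 6 | 0.81 | 1.05 | 1.24 | 1.48 |
| Change | 5 vs 5 | 0.91 | 1.18 | 1.39 | 1.66 |

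For week 3 alone with 15 vs 15: 1.701 × 1 × √(2/15) = 1.701 × 0.365 = 0.62 SD. Adding a period term costs one degree of freedom (28 to 27). If the arms are balanced within period, the half-width is 1.703 × 0.365, still 0.62 SD.

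The change and week-3 figures describe different quantities. Their ratio is not a gain in efficiency.

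**The case against.** The best defence is that the change contrast is a comparison of randomised treatments and has a meaning. Two of the three CDX-1127 doses fall between the biopsies, so it estimates an effect of CDX-1127 on the day 22 to day 85 course, at least among those with pairs. Section 7.5 openly restricts it to people with a week-12 biopsy. The trial sets out to estimate rather than test, and no decision depends on this endpoint. All of that stands, and it limits the consequence. It does not make the contrast an answer to secondary objective 1.

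A reader might infer more than the documents support:

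- **That the arms are compared on FoxP3 nowhere else.** Circulating FoxP3+ regulatory T cells are an endpoint under secondary objective 2a, and Section 7.5 plans repeated-measures models by arm for them. The gap concerns the vaccine site.
- **That the change says nothing about CDX-1127.** It estimates an effect on change. The null and wrong-sign results depend on a week-3 effect, for which the documents give no vaccine-site data.
- **That the week-3 biopsies go unused.** Paired ones enter the change, Section 7.1.2 keeps week-3 FoxP3 as a parameter, and Section 6.7.3 lists assays that may be run. What is missing is a specified between-arm FoxP3 analysis for the unpaired ones.
- **That week 3 is more precise by a known amount.** With 8 vs 7 pairs, the change interval would match 0.62 SD at a correlation of about 0.77: 0.917 × √(2 × 0.23) = 0.62. The pair count is unknown as well.

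One further objection stands against a simple pooled week-3 analysis. Section 5.2.1 moves the vaccine from half intradermal to fully subcutaneous at the amendment, and the samples are skin punches, so period has to be taken into account.

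**Conclusion.** The mismatch is real and follows from the text of Sections 2.2, 5.3.1, 7.5 and 9.1 without any assumption: the planned contrast is the week-12 effect minus the week-3 effect, and it does not estimate the effect on FoxP3+ level at either visit. The pairs are confined to a pre-amendment subset selected after randomisation, and week-3 biopsies without a pair have no pre-specified between-arm FoxP3 analysis.

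The size depends on inputs that the documents do not supply. With at most 15 pairs, the 90% CI half-width for the change is 0.71 to 1.30 SD over correlations from 0.7 to 0; with 5 vs 5 pairs it is 0.91 to 1.66 SD. A week-3 comparison with 15 evaluable per arm would have about 0.62 SD. The case for week 3 rests on its being the quantity asked about, in the participants as randomised, and not on these widths. The point affects one secondary objective and leaves the primary endpoints untouched. It should be corrected because the stated analysis can mislead and the remedy is cheap.

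**What to change.** In Section 7.5, make the main analysis for secondary objective 1 the Arm A − Arm B difference in day-22 FoxP3+ CD4+ cells per mm², with a 90% CI, on the log scale if the data are skewed. Include every participant with an evaluable day-22 biopsy, and report the number without one by arm. Adjust for, or stratify by, enrolment before or after v12-03-2020, because the vaccine route changed then.

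Report week-12 levels by arm and the week 3 to week 12 change descriptively in the pre-amendment subset. Give the number of pairs per arm and the reasons for missing week-12 biopsies, and state that the change measures the difference between the two visits' effects.

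The cost is revised wording, a small amount of extra analysis and one degree of freedom for period. No new samples are needed.
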